### **Special Precautions**

Subjects should receive KN046 and KN026 infusion in a medical institution equipped with resuscitation equipment and emergency medicine, and stay in the hospital for observation for at least 2 hours after the end of each infusion. Whenever a subject receives KN046 and KN026 infusion, it must be ensured that the subject's infusion-related reactions or severe hypersensitivity reactions can be urgently handled according to local treatment guidelines. In order to ensure timely treatment of possible allergic reactions, the study site must always have appropriate rescue medications, such as dexamethasone 10 mg, epinephrine (1:1000 dilution) or alternative drugs, and assisted ventilation equipment.

KN046 and KN026 infusion should be stopped immediately in the event of  $\geq$  Grade 2 hypersensitivity, inflammatory, or allergic reactions.

NCI recommendations for the treatment of infusion-related reactions, severe hypersensitivity reactions, and oncolytic syndrome, are provided in Sections 6.2.3.1 and 6.2.3.4, respectively.

### ***Infusion-Related Reactions and Hypersensitivity Reactions***

Symptoms of infusion-related reactions may be fever, cold intolerance, chills, sweating, and headache. Infusion-related reactions can be handled as described in Table 4.

Potential risk factors for infusion-related reactions may include:

- Elderly
- Female
- History of anaphylaxis or history of drug allergy
- Atopic dermatitis or asthma
- Concomitant medications, including beta agonists, angiotensin-converting enzyme inhibitors (ACEIs), or nonsteroidal anti-inflammatory drugs (NSAIDs).

**Table 4 Handling of Infusion-related Reactions Caused by KN046 and KN026**

| NCI-CTCAE Grade                                                                                                                                                                                                                                                                                           | Dose Modification of KN046 or KN026                                                                                                                                                                                                                                                                               |
|-----------------------------------------------------------------------------------------------------------------------------------------------------------------------------------------------------------------------------------------------------------------------------------------------------------|-------------------------------------------------------------------------------------------------------------------------------------------------------------------------------------------------------------------------------------------------------------------------------------------------------------------|
| Grade 1 - Mild
Mild transient reaction; infusion interruption not required; intervention not required.                                                                                                                                                                                          | 
 
Decrease the infusion rate of KN046 or KN026 by 50% and closely monitor for any signs of worsening
 
                                                                                                                                                              |
| Grade 2 - Moderate
Treatment interruption or infusion required, and prompt symptomatic treatment (e.g., antihistamines, NSAIDs, anesthetics, IV fluids)                                                                                                                                         | 
 
Discontinue infusion with KN046 or KN026
 
Resume infusion after resolution of infusion-related reaction or decrease in severity to at least Grade 1, with the infusion rate of 50% of the original rate
 
Closely monitor for signs of worsening
 
 |
| Grade 3 or 4-Severe or life-threatening
Grade 3: Prolonged (e.g., not rapidly responsive to symptomatic medication and/or interruption of infusion); recurrence of symptoms following improvement; hospitalization due to AEs
Grade 4: Life-threatening, urgent intervention required | 
 
Immediately discontinue infusion with KN046 or KN026 and disconnect the subject's infusion line
 
Subjects must immediately discontinue treatment with KN046 or KN026 and must not receive any KN046 or KN026 treatment again
 
                            |

Treatment with KN026 or KN046 is recommended to be discontinued if a  $\geq$  Grade 2 infusion-related reaction reappears after administration of prophylaxis; if the investigator assesses that the subject can also benefit from KN026 or KN046 treatment, the drug may be continued after discussion with the sponsor.

For sterility reasons, the drug should be used immediately after preparation within 8 hours from the completion of the preparation to the completion of the infusion.

NCI-CTCAE = National Cancer Institute-Common Terminology Criteria for Adverse Events

If an infusion-related reaction occurs with the first dose of KN026, prophylaxis, including combinations of H1- and H2-blocker antihistamines (e.g. diphenhydramine and cimetidine) and NSAIDs (e.g., acetaminophen), will be administered over 90 minutes ( $\pm$  15 minutes) at 30 to 60 minutes ( $\pm$  15 minutes) prior to each subsequent dose. In case of infusion reactions, the details of drug preparation and infusion must be recorded. After the 5th dose, the duration of dosing may be shortened at the discretion of the investigator.

Slow infusion of KN046 is strongly recommended for the first 6 doses and prophylactic medications should be given 30 to 60 minutes prior to the first 4 KN046 infusions. Prophylactic medications include combination of H1- and H2-blocker antihistamines (e.g., diphenhydramine and cimetidine) and NSAIDs such as acetaminophen. The recommended prophylactic regimen includes diphenhydramine 25 to 50 mg IM or equivalent PO, cimetidine 400 mg IV infusion, and acetaminophen 500-1000 mg PO. Steroids are generally not recommended as part of routine prophylactic regimens, and are used only if necessary. Montelukast may be included in the prophylactic regimen if the patient experiences symptoms of spasm bronchial. If there is no infusion-related reaction after the 4th infusion, prophylactic medications for subsequent doses should be administered at the discretion of the investigator. In vitro studies showed that KN046 caused strong immunostimulatory effects. In combination with platinum-based doublet chemotherapy, a certain proportion of infusion-related reactions and increased inflammatory

factors (IL-6, IL-10) were observed after Dose 2 of KN046; the proportion of infusion reactions decreased rapidly with the increased number of doses. For subjects who experience  $\geq$  Grade 2 treatment-related AEs of KN046 after Dose 1, it is recommended to determine IL-6 levels before the next dose. If IL-6 levels increase, pretreatment with tocilizumab 160 mg (intravenous infusion 1-2 hours prior to KN046 administration) is allowed after consultation with the sponsor's Medical Department; for subjects who experience  $\geq$  Grade 2 IRRs during the administration of KN046, it is recommended to determine IL-6 levels immediately, and 160 mg tocilizumab treatment is allowed on the basis of routine clinical management. After IRR recovery, resuming slow KN046 administration (at least 50% reduction in infusion rate) under respiratory, ECG, and blood pressure monitoring conditions is allowed.

Severe hypersensitivity reactions could manifest as airway injury, decreased oxygen saturation (less than 90%), confusion, lethargy, hypotension, pale skin/clamminess, and cyanosis.

If severe hypersensitivity reactions occur, subjects should be monitored immediately and injected with epinephrine and dexamethasone, and the ICU should be notified and transferred if required. Specific management principles can be found in the full version of the Emergency Treatment of Anaphylactic Reactions: Guidelines for Healthcare Providers (UK) at <https://www.resus.org.uk/pages/reaction.pdf> (Reference: Emergency Treatment of Anaphylactic Reactions: Guidelines for Healthcare Providers, 2008).

If a subject experiences an infusion-related reaction or hypersensitivity reaction, the investigator is advised to collect plasma histamine, IL-6, and C-reactive protein (CRP) within 30 minutes of symptom onset, and collect urine methylhistamine again within 24 hours after symptom onset, as well as unplanned ADA and PK samples. For subjects with chest pain, ECG, myocardial enzymogram (CPK, CK, TnI, TnT), and BNP should be done within 30 minutes of symptom onset. Serum complements (C3, C4, CH50) are required for subjects with typical or atypical manifestations of "triad", such as arthralgia, rash, and/or gastrointestinal symptoms.

Note: Patients with suspected anaphylaxis should not attempt additional premedication or re-dosing after slowing down the infusion rate. If, in the opinion of the investigator, the benefit of continuing KN046 treatment outweighs the risk to the patient, the investigator is encouraged to discuss with the sponsor and to reach consensus on the rechallenge of the desensitization regimen and/or an appropriate premedication regimen.

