- Other HER2-positive solid tumors: **Have received**  $\geq$  1st line systemic therapy for metastatic or locally advanced unresectable tumors and have disease progression, have received the standard of care without unequivocally prolonged survival, or have refused standard of care after the 1st line systemic therapy; front-line systemic therapy for ESCC and mCRC includes at least platinum in combination with fluorouracil or taxane-based chemotherapy; mCRC requires  $\geq$  2 lines of systemic therapy for metastatic or locally advanced unresectable tumor with disease progression; front-line systemic therapy for ovarian and cervical cancer includes at least platinum (cisplatin or carboplatin) -based chemotherapy; subjects who have relapsed within 6 months after the end of neoadjuvant/adjuvant platinum-containing chemotherapy are considered to have failed 1 line of therapy;
- I05. At least 1 measurable lesion at baseline per RECIST 1.1 criteria. If a subject has only 1 measurable lesion at baseline, the lesion area must have not received prior radiotherapy, or there is evidence of significant progression of the lesion after the end of radiotherapy;
- I06. ECOG score 0 or 1 (Appendix 5);
- I07. LVEF  $\geq$  50%, determined by echocardiography (ECHO); multiple uptake gated acquisition (MUGA) scan will be used only in the absence of ECHO, and baseline and subsequent follow-up methods will be the same;
- I08. Liver function meets the following criteria within 7 days prior to the first dose:
- Total bilirubin  $\leq 1.0 \times \text{ULN}$  (Gilbert's syndrome or total bilirubin of subjects with liver metastasis  $\leq 1.5 \times \text{ULN}$ );
  - Transaminase (ALT/AST)  $\leq 1.5 \times \text{ULN}$  ( $\leq 3 \times \text{ULN}$  for subjects with liver metastases);
- I09. Renal function within 7 days prior to the first dose: Serum creatinine  $\leq 1.5 \times \text{ULN}$  and serum creatinine clearance  $\geq 60 \text{ mL/min}$  (calculated according to the Cockcroft-Gault formula);
- I10. Bone marrow function meets the following criteria within 7 days prior to the first dose:
- Hemoglobin  $\geq 90 \text{ g/L}$ ;
  - Absolute neutrophil count  $\geq 1.5 \times 10^9 /\text{L}$ ;
  - Platelet count  $\geq 100 \times 10^9/\text{L}$ ;
  - INR or PT  $\leq 1.5 \times \text{ULN}$  and aPTT  $\leq 1.5 \times \text{ULN}$ ;
- I11. TSH is normal; if TSH is abnormal, total T3 or free T3, and free T4 should be within the normal range;

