| Infusion-related Reactions            |                                                                                                                                                                                                                     | See Section 6.2.3.1                                                                                                                                                                                                                                                         |
| Drug-related Laboratory Abnormalities | Grade 3 leukopenia or neutropenia                                                                                                                                                                                   | Continue dosing after recovery to $\leq$ Grade 1                                                                                                                                                                                                                            |
|                                       | Grade 2 ALT, AST, or TBIL increased for patients with normal baseline ALT, AST, or TBIL;
Grade 3 or 4 ALT, AST, or TBIL increased lasting $< 7$ days for patients with baseline ALT, AST, or TBIL $> \text{ULN}$ | Dose Interrupted
Resume the treatment if ALT, AST, or TBIL decreased to $\leq$ Grade 1.                                                                                                                                                                                  |
|                                       | Grade 3 ALT, AST, or TBIL increased lasting $\geq 7$ days or Grade 4 ALT, AST, or TBIL increased                                                                                                                    | Permanent discontinuation                                                                                                                                                                                                                                                   |

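### Two KN026 redosing rules are each internally inconsistent: a brief Grade 4 liver-test rise with baseline above ULN (Table 3), and a Grade 2 infusion reaction that recurs as Grade 3–4 (Table 4 and its note)

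*Protocol*

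**What the plan says.** **Liver tests, KN026 (Section 6.1.4.2, Table 3).** One row covers two situations. The second is "Grade 3 or 4 ALT, AST, or TBIL increased lasting" less than 7 days in patients whose baseline value is above ULN. The action is to interrupt KN026 and then "Resume the treatment if ALT, AST, or TBIL decreased to" Grade 1 or lower. The next row orders permanent discontinuation for a Grade 3 rise of at least 7 "days or Grade 4 ALT, AST, or TBIL increased". Its Grade 4 limb carries no condition on duration or baseline.

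**Infusion reactions (Section 6.2.3.1, Table 4).** For Grade 3 or 4 the table says "Subjects must immediately discontinue treatment with KN046 or KN026 and must not receive any KN046 or KN026 treatment again". The note directly below recommends discontinuing KN026 or KN046 if a Grade 2 or higher "infusion-related reaction reappears after administration of prophylaxis". It adds that, where the investigator sees benefit, "the drug may be continued after discussion with the sponsor". The note has no upper grade limit.

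**Related text.** The infusion-reaction line of Table 3 says only "See Section 6.2.3.1". For KN046, Section 6.1.4.1 lets the investigator and Medical Monitor discuss a recurrent infusion reaction, but expressly leaves out Grades 3 and 4.

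**The concern.** These are stopping rules for severe or life-threatening toxicity, so a site should be able to read one answer from them. In the liver-test case the two rows give opposite final actions, and neither calls for contact with the sponsor. Two sites could both follow the protocol and treat the same patient differently. In the infusion-reaction case an absolute ban sits above a permission that, read literally, reaches the banned grades.

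The first consequence is for subject safety. The second is for the tolerability analysis in Section 9.6.1, which counts subjects with interruption, delay and discontinuation. The same event could be counted as an interruption at one site and a discontinuation at another. Dosing rules belong to the protocol, so a statistical analysis plan would not settle either question.

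**Working it through.** The check is textual: find a subject who meets both instructions, then see whether other text decides between them.

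**(a) Table 3, liver tests**

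1. Case: KN026-related ALT, AST or bilirubin rise, Grade 4, under 7 days, baseline above ULN.
2. Resume row: Grade 3 or 4, under 7 days and baseline above ULN are all met. Action: interrupt, resume at Grade 1 or lower.
3. Stop row: Grade 4 is met, and nothing else is required. Action: permanent discontinuation.
4. Can it occur? Yes. Inclusion criterion I08 admits ALT/AST up to 1.5 × ULN, and up to 3 × ULN "for subjects with liver metastases". Bilirubin may reach 1.5 × ULN with Gilbert's syndrome or liver metastases.
5. Does other text decide? No. Table 3 writes out its Grade 4 exceptions (isolated amylase or lipase, electrolytes, alkaline phosphatase with bone metastases), but they attach to the row for other Grade 4 events. None covers ALT, AST or bilirubin.

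**(b) Table 4 and its note, infusion reactions**

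1. Case: a Grade 2 reaction to the first KN026 dose, prophylaxis before later doses, then a Grade 3 or 4 reaction.
2. Table 4: the second reaction is Grade 3–4. Action: no further drug.
3. Note: a reaction of Grade 2 or higher has reappeared after prophylaxis. Action: stopping is recommended, and continuing is allowed after talking to the sponsor.
4. Can it occur? Yes. Table 4 lets the infusion resume at half rate after a Grade 2 reaction, and Section 6.2.3.1 calls for prophylaxis before each later KN026 dose if the first dose caused a reaction. A first reaction of Grade 3–4 does not create the conflict, because it already ends treatment.
5. Does other text decide? For KN046, Section 6.1.4.1 does. For KN026, Table 3 only points back to Section 6.2.3.1, where the conflict lies.

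**Size**

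- Section 1.3.3 describes four related events of Grade 3 or above among 63 subjects on KN026 alone, all Grade 3. That is 0 of 63 with a related Grade 4 event. The exact two-sided 95% upper limit is 1 − 0.025^(1/63) = 5.69%.
- If that rate applied here, the upper limit for *any* related Grade 4 event would be 80 × 0.0569 = 4.5 to 122 × 0.0569 = 6.9 subjects. Case (a) also needs a liver test, a duration under 7 days and a raised baseline, so it is a subset of unknown size.
- For (b), the same study describes one Grade 3 infusion reaction. It occurred on the first dose, so it was not a recurrence. The protocol gives no rate for a second reaction of Grade 3–4.
- The combination study in Section 1.4.3 does not separate Grade 4 from Grade 3.

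**The case against.** The strongest reply concerns the infusion reactions. The note's default is also to stop, and continuing is only a permission after sponsor discussion, so a site that stops satisfies both texts. A specific ban would not normally yield to a general permission printed below it, and Section 6.1.4.1 shows what the sponsor intended for KN046. This stands in part. It makes (b) milder than (a), because the sponsor is consulted before any redosing, and it confines the practical gap to KN026. It does not reconcile a ban with a permission that covers the same grades, and nothing in the KN026 text tells the sponsor or the site that Grade 3–4 is outside the discussion.

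For (a), one could treat the narrower resume row as an implied exception to the stop row. No text says so, and the table writes out its other Grade 4 exceptions.

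A reader might infer more than the documents support:

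- *That the infusion-reaction conflict is equally open for both drugs.* Section 6.1.4.1 closes it for KN046 in substance, although the note itself still names both.
- *That a Grade 1 first reaction is enough.* The note speaks of a Grade 2 or higher reaction reappearing, so its natural reading needs an earlier reaction of at least Grade 2.
- *That neighbouring text adds further contradictions.* The KN026 list of further grounds for considering a permanent stop supplements Table 3. The slow KN046 resumption sentence in Section 6.2.3.1 can be read as restating the Grade 2 row. The KN046 rechallenge note after suspected anaphylaxis requires consensus with the sponsor and is not shown to override Table 4. The LVEF resume test in Table 6 may be intended. The LVEF reporting wording in Table 1 footnote 4 and Section 8.2 is garbled, but Section 8.2.2 captures the events.

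**Conclusion.** The point holds for KN026. The Table 3 overlap is plain on the face of the text: two rows, one patient, opposite final actions. The Table 4 overlap also holds, on the path from Grade 2 through prophylaxis to Grade 3–4, and is tempered by the sponsor discussion. Each rule is inconsistent within itself; the liver rule and the infusion rule do not conflict with each other.

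Few subjects are likely to be affected. No case count follows from the documents: the limit of 4.5 to 6.9 subjects covers a wider class of events and assumes that the monotherapy rate carries over to the combination. The definitions and analyses of ORR and DOR and the sample size do not depend on these rules. The case for acting rests on the severity of the events and the ease of correction, not on their number.

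**What to change.** 1. **Table 3.** Delete *or 4* from the row for rises under 7 days with baseline above ULN. This matches the table's general Grade 4 stop. If the medical team means to allow resumption after a brief Grade 4 rise in these patients, exempt that case expressly in the permanent-discontinuation row instead.
2. **Note below Table 4.** Change Grade 2 or higher to Grade 2.
3. **Section 6.2.3.1.** Add one sentence stating that Table 4's Grade 3–4 ban prevails for both drugs. If the KN046 rechallenge in the closing note is to remain available after such a reaction, name it there as the sole exception.

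The cost is a clarifying amendment to one table row and one note, one added sentence, and a letter to sites. Neither the sample size nor the data collection changes.

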### ***Pulmonary Toxicity***

Patients receiving HER2-targeted therapy may develop pneumonitis, including asymptomatic pneumonitis, which is only radiologically detected (CTCAE Grade 1) and symptomatic pneumonitis (pneumonitis with CTCAE Grade 2 does not affect daily activities, or CTCAE Grade 3 pneumonitis affects daily activities and patients require oxygen). To monitor asymptomatic pneumonitis (CTCAE Grade 1), a chest CT scan is required. Additional chest X-rays or CT scans are required clinically. If pneumonitis progresses, consultation with a pulmonologist is required. If a patient develops Grade 3 pneumonitis, KN026 should be withheld and the patient should be treated accordingly by a physician (e.g., short course of hormonal therapy, oxygen inhalation, etc.). Management of pneumonitis is presented in Table 5.

**Table 5 Management of Pneumonitis due to KN026**

| CTCAE Grade | Medical Examination Required                                                                                                                                                                                                                                                                                                                                                  | Management of Pneumonia                                                                                                                                              | Dose Modification of KN026                                                                                                                                                                                                                                                                                                                                             |
|-------------|-------------------------------------------------------------------------------------------------------------------------------------------------------------------------------------------------------------------------------------------------------------------------------------------------------------------------------------------------------------------------------|----------------------------------------------------------------------------------------------------------------------------------------------------------------------|------------------------------------------------------------------------------------------------------------------------------------------------------------------------------------------------------------------------------------------------------------------------------------------------------------------------------------------------------------------------|
| Grade 1     | 
 
Lung CT scans, and required pulmonary function testing includes: spirometry, DLCO, and oxygen saturation at rest.
 
Chest X-ray or CT scan will be repeated every 6 weeks until return to baseline.
 
                                                                                                                  | 
 
Exclude source of infection
 
No special treatment is required
 
                                              | 
 
Maintain the original dose
 
                                                                                                                                                                                                                                                                                           |
| Grade 2     | 
 
Lung CT scans, and required pulmonary function testing includes: spirometry, DLCO, and oxygen saturation at rest.
 
Repeat chest X-ray or CT scan every 3 to 4 weeks (in a treatment cycle) until return to baseline.
 
                                                                                                | 
 
Exclude source of infection
 
Hormonal therapy if cough is evident
 
                                          | 
 
Resume the original dose of KN026 after recovery to <math>\leq</math> Grade 1. If cough persists, hold KN026 until recovery to <math>\leq</math> Grade 1.
 
Permanently discontinue KN026 if the subject fails to recover to <math>\leq</math> Grade 1 within 3 weeks after appropriate medical intervention.
 
 |
| Grade 3     | 
 
Lung CT scans, and required pulmonary function testing includes: spirometry, DLCO, and oxygen saturation at rest.
 
Repeat chest X-ray or CT scan every 3 to 4 weeks (in a treatment cycle) until return to baseline.
 
Consultation with a pulmonologist for bronchoscopy (biopsy or bronchoalveolar lavage)
 
 | 
 
Exclude source of infection
 
Administer hormonal therapy and gradually reduce the dose as medically judged
 
 | 
 
Hold KN026 until recovery to <math>\leq</math> Grade 1.
 
If a subject has clinical benefit, the original dose of KN026 can be maintained (recovered to <math>\leq</math> Grade 1 within 3 weeks) after recovery to <math>\leq</math> Grade 1.
 
                                                                |
| Grade 4     | 
 
Lung CT scans, and required pulmonary function testing includes: spirometry, DLCO, and oxygen saturation at rest.
 
Repeat chest X-ray or CT scan every 3 to 4 weeks (in a treatment cycle) until return to baseline.
 
Consultation with a pulmonologist for bronchoscopy (biopsy or bronchoalveolar lavage)
 
 | 
 
Exclude source of infection
 
Administer hormonal therapy and gradually reduce the dose as medically judged
 
 | 
 
Permanently discontinue KN026
 
                                                                                                                                                                                                                                                                                        |

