**Dose Modification of KN026**

Whenever a subject experiences a protocol-specified  $\geq$  Grade 3 toxicity related to KN026 treatment (except for laboratory abnormalities that are not clinically significant or do not meet the criteria for AEs listed below), KN026 is required to be interrupted until the treatment-related toxicity resolves to  $\leq$  Grade 1. Guidelines for dose modification of KN026 are provided in Table 3.

To monitor asymptomatic pneumonitis (CTCAE Grade 1), a chest CT scan is required. Additional chest X-rays or CT scans are required clinically. Management and dose modification of pneumonitis suspected to be related to KN026 are provided in Section 6.2.3.2.

LVEF and cardiovascular-related clinical symptoms and signs need to be monitored during treatment with KN026. Management and dose modification of cardiotoxicity suspected to be related to KN026 are described in Section 6.2.3.3.

If KN026 is discontinued due to an AE, the investigator should decide whether to continue treatment with KN046 in accordance with Section 6.1.4.1.

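### Table 5 does not settle whether KN026 is given during Grade 2 pneumonitis without persisting cough: one sentence presupposes a stop that nothing orders, and the next makes the hold conditional on cough

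*Protocol*

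**What the plan says.** The KN026 dose column of Table 5 (Section 6.2.3.2, Pulmonary Toxicity) gives these instructions:

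- Grade 1: "Maintain the original dose".
- Grade 2, first sentence: "Resume the original dose of KN026 after recovery to" Grade 1 or lower.
- Grade 2, second sentence: "If cough persists, hold KN026 until recovery to" Grade 1 or lower.
- Grade 2, further bullet: "Permanently discontinue KN026 if the subject fails to recover to" Grade 1 or lower within 3 weeks of appropriate medical intervention.
- Grade 3: "Hold KN026 until recovery to" Grade 1 or lower.
- Grade 4: permanent discontinuation.

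The paragraph introducing the table says "If a patient develops Grade 3 pneumonitis, KN026 should be withheld" and gives no dosing instruction for Grade 2. The general rule under Dose Modification of KN026 (Section 6.1.4) applies to related toxicity of Grade 3 or higher: "KN026 is required to be interrupted until the treatment-related toxicity resolves to" Grade 1 or lower. For pneumonitis the same section hands over: "Management and dose modification of pneumonitis suspected to be related to KN026 are provided in Section 6.2.3.2". Table 3 also refers pulmonary toxicity to Section 6.2.3.2.

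**The concern.** Grades 1, 3 and 4 each have an explicit opening instruction: continue, hold, or stop for good. Grade 2 has none. It opens with the condition for restarting, then makes a hold depend on cough. A site with a Grade 2 subject who has no persisting cough can follow the first sentence and withhold KN026 until recovery, or follow the second and give the next dose. Both choices can be defended from the text.

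This matters first for the subject, since the decision is whether to re-expose someone with unresolved pneumonitis. It also matters for the safety results. Dose interruptions, delays and discontinuations are the protocol's tolerability measure, summarised by cohort (Section 9.6.1, Tolerability). They also feed the provision in Section 6.1.4 under which permanent discontinuation may be considered after more than 9 weeks of cumulative delay or more than 3 interruptions. For this event those counts could partly reflect how a site read one table cell.

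**Working it through.** The check is mainly textual, because the point rests on no planned figure.

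**Step 1: take each Grade 2 sentence as the operative rule.**

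| Grade 2 subject | First sentence governs | Second sentence governs |
|---|---|---|
| Cough persists | KN026 off until Grade 1 or lower | KN026 off until Grade 1 or lower |
| Cough does not persist | KN026 off until Grade 1 or lower | No hold ordered |
| Sentence left without work | The cough sentence is redundant | The restart sentence has nothing to restart from when there is no cough |

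The sentences agree on the recovery threshold, and they agree when cough persists. They part only for Grade 2 without persisting cough.

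**Step 2: look for a passage that decides that case.** The introductory text of Section 6.2.3.2 states withholding at Grade 3 and says nothing on Grade 2 dosing. The general rule in Section 6.1.4 requires interruption from Grade 3 and sends pneumonitis to Section 6.2.3.2, as does Table 3. Every cross-reference ends at the unclear cell.

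**Step 3: how many doses are in question.** KN026 is given every 3 weeks after the Cycle 1 Day 8 loading dose, and the discontinuation limit is 3 weeks. So 3 weeks ÷ 3 weeks per dose = about 1 scheduled dose. In Cycle 1, with doses in Weeks 1, 2 and 4, a 3-week span starting just after the first dose could take in two. The limit runs from appropriate medical intervention, and this row makes hormonal therapy depend on evident cough. Without cough, the start of the 3 weeks is therefore itself not well fixed.

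**Step 4: how many subjects.** Section 1.3.3 reports one Grade 2 interstitial pneumonia SAE related to KN026 among 63 monotherapy subjects: 1/63 = 1.6%, exact 95% CI 0.04% to 8.5%. Applied to the planned 80 to 122 subjects:

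- Point estimate: 80 × 1/63 = 1.3; 122 × 1/63 = 1.9.
- Upper limit: 80 × 0.085 = 6.8; 122 × 0.085 = 10.4.

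This is a rough indicator only. It counts a serious event, so non-serious Grade 2 cases are not in it. It also does not separate subjects with and without persisting cough, and the disputed group is the latter.

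**The case against.** The strongest reply is that the two sentences can be read together: KN026 is off at Grade 2, restarts on recovery, and stays off while cough persists. The word persists fits a hold already in place, and the treatment column of the same row already mentions evident cough. On this reading the second sentence is merely redundant. The reading is possible, but it supplies a hold at onset that no sentence in the protocol orders, so it does not close the gap.

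It is also fair that naming Grade 3 in Sections 6.1.4 and 6.2.3.2 does not say that dosing continues at Grade 2. That would be inference from silence, and Table 3 itself interrupts KN026 for certain Grade 2 liver abnormalities. These sections therefore leave Grade 2 open; they do not prove that dosing continues.

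Four stronger readings are tempting and are not supported:

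- A reader might infer that the table restricts the hold to subjects with cough. The cell makes a hold conditional on cough but contains no word of exclusivity. The defect is an internal inconsistency that leaves one case open; the two sentences do not conflict for every Grade 2 subject.
- A reader might infer opposite decisions at every visit until recovery. The three-weekly schedule and the 3-week limit confine the question to about one dose.
- A reader might take the 1.3 to 1.9 above as the expected number of affected subjects. It is neither a Grade 2 incidence nor a count of the disputed subset.
- A reader might add KN046's own pneumonitis risk to the argument. Table 5 governs KN026 only, and KN046 toxicity has separate rules in Section 6.1.4 and Appendix 4.

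**Conclusion.** The point holds in a limited form. The Grade 2 cell of Table 5 presupposes a stop it does not order and then makes a hold conditional on persisting cough. Nothing elsewhere in the protocol decides whether KN026 is given in Grade 2 pneumonitis without persisting cough. The undetermined window is about one scheduled dose per affected subject, assuming the 3-week limit starts near onset. Affected subjects are likely to be few, but the documents give no figure for them. That sites would in fact dose differently is a possibility the wording allows; nothing in the documents shows it.

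The sample size and the ORR and DOR analyses are untouched. Because the gap concerns dosing in a named toxicity and costs little to close, it should be corrected.

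**What to change.** Reconcile the two sentences of the Grade 2 row with each other, with the introductory text of Section 6.2.3.2 and with the general KN026 rule in Section 6.1.4, so that one rule states whether and when KN026 is held at Grade 2. Which rule applies is for the clinical team to decide.

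No extra eCRF item is needed. Section 8.2 already requires each AE report to record action taken, including delay or discontinuation of study drug, and Section 9.6.1 already lists reasons for interruption, delay and discontinuation.

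The cost is amendment wording in one table row, with matching text in the two sections if needed, and no added subjects or procedures.
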